#### Participant timeline {13}

Participant timeline is outlined in Table 1.

**Table 1 Tab1:** Schedule of assessments and study procedures

	Study period										
	**1–6 weeks until surgery**	**D-3**	**D-2**	**D-1**	**D0**	**D1**	**D2**	**D3**	**D30**	**D90**	**D180**
	Outpatient clinic	Home		Hospital					Home		
Screening study eligibility	x										
Advising pregnancy test if applicable	x										
Information on PERSuaDER, study content and consent	x										
Collection informed consent	x										
Randomization	x										
Dispersion and instruction on intervention medication	x										
SDD intervention		x	x	x	x	x	x	x			
Patient diary		x	x	x	x	x	x	x			
Resectional specimen swabs					x						
Pneumonia assessment									x	x	x
Other complications assessment*									x	x	x
Medication adherence assessment									x		
QoL questionnaires	x								x	x	x
Other secondary outcome assessment*									x	x	x
(S)AE, SUSAR assessment **		x	x	x	x	x	x	x	x	x	x

* Other secondary outcomes: postoperative length of stay, the intensive care unit (ICU) length of stay, re-admissions, cost assessment. ** As described in the “Adverse event reporting and harms {22}” section*. QoL*, Quality of Life; *(S)AE*, (Serious) Adverse Event; *SUSAR*, Suspected Unexpected Serious Adverse Event

### Sample size {14}

Based on contemporary registries and literature, we assume an incidence of postoperative pneumonia in the control group of approximately 22% [27]. The sample size calculation is based on the primary objective of the trial to demonstrate that the intervention will result in a clinically relevant decrease of postoperative pneumonia by 40%. This would convey to an incidence of 13% (superiority) with 90% power and a two-sided alpha of 0.05. A group-sequential design is used with two interim analyses at 30% and 60% and two-sided asymmetric bounds (Hwang-Shih-DeCani spending function) for superiority and futility. The calculated sample size convenes to a total sample size of 814 study participants (407 per arm). Despite the short study intervention, some early deaths may occur and surgeries may be canceled in this time frame after randomization. Therefore, we anticipate a 5% loss to follow-up rate and will add 20 additional subjects to each group to compensate for this. As such, a total sample size of 854 participants will be required.

### Recruitment {15}

To recruit 854 patients for the study at a realistic, expected recruitment rate of ~35%, we will recruit patients for 39 months to draw from a source population of approximately 2681 patients. Therefore, we are likely to recruit the planned number of patients from the defined source population. In case of stagnating inclusion, other centers with the intention to participate will be added to this study by amendments.

### Assignment of interventions: allocation

#### Sequence generation {16a}

After confirmation of eligibility and completion of IC, randomization will be performed by the local research staff by using the built-in randomization module; the sequence (concealed within castoredc.com) will be initiated by the site study data manager, independent of the investigators and clinical staff using block randomization with variable block size, stratified by the three main confounding factors in esophageal surgery: hospital, site of anastomosis, and Charlson Comorbidity Index. Participants are allocated in a 1:1 ratio to receive either usual care alone or usual care plus the SDD treatment policy.

### Concealment mechanism {16b}

Randomization will be performed by the local research staff through the built-in randomization module in Castor EDC (www.castoredc.com), and the sequence (concealed within Castor EDC) will be initiated by the study data manager, independent of the investigators and clinical staff.

### Implementation {16c}

Eligible patients will be identified at the outpatient clinic of the surgeon. Patients will be informed about the goals of the study, its risks and benefits after which informed consent will be obtained. The intervention will be assigned by the local research staff through a randomization program (Castor EDC).

## Assignment of interventions: blinding

### Who will be blinded {17a}

As an open label study, allocation of the intervention will not be blinded. Analysis of the outcome parameters will be blinded.

### Procedure for unblinding if needed {17b}

N/A as an open label study, the allocation of the intervention will not be blinded. The analysis of the outcome parameters will be blinded.

### Data collection and management

#### Plans for assessment and collection of outcomes {18a}

During the outpatient visit at which inclusion takes place, the patient will be assigned an anonymized participation number. The key needed to identify the patient data is held by the Principal Investigator (PI) of the participating sites. During the trial, data will be collected by delegated research personnel, who are listed in the delegation log. Data for the primary, and most secondary endpoints will be collected from the patient’s medical records. Data on secondary endpoints regarding quality of life and other patient-derived outcome measures (i.e., patient diary) will be collected through questionnaires (paper-based or through CastorEDC). Data on IMP accountability will be gathered from patient medical records, patient diary, and a dedicated IMP-accountability form. This data will be entered into the electronic case report forms (eCRF). Data such as source documents will be maintained at the participating site for 25 years after the end of this study, conforming to European Union Clinical Trials Regulation (EU-CTR).

### Plans to promote participant retention and complete follow-up {18b}

To ensure participant retention and complete follow-up, a commitment has been agreed upon for the local researchers. They will contact the patients regarding the completion of the questionnaires throughout the follow-up period (Fig. 1). Patients who have enrolled in the study are at liberty to withdraw from study participation at any moment. Participants that have withdrawn from the study will not be replaced. Participants who wish to drop out of the study during follow-up will be analyzed according to the intention-to-treat principles.

### Data management {19}

The study will utilize eCRF for data collection. All data will be collected and processed in accordance with the General Data Protection Regulation (EU) 2016/679. All site staff will be trained on correct eCRF completion. Study subjects will be identified only by their unique subject number which will be used in all correspondence and further administration in the study database. The investigator and the investigation site team shall maintain patient confidentiality in all documentations. An identification log will be kept of all subject numbers linked to corresponding participants. The list will remain at the participating site. Data validation will be performed by checking the eCRFs with the medical records of all trial patients on the primary outcome by the monitor. Discrepancies will be discussed with the study nurse or site investigator. Study-related documents, patient records, signed informed consent forms, and source documents will be maintained at the participating site for 25 years after the end of this study, conform EU CTR. Source data will be entered in the online database Castor and afterwards exported for the analyses.

### Confidentiality {27}

Information obtained during the study will be regarded as confidential. The investigator and all members of the study team agree not to disclose or publish such information in any way to any third party without prior written permission from the principal investigator, which will not be unreasonably withheld, except as required by law. The investigator will take all measures to ensure patient confidentiality.

### Plans for collection, laboratory evaluation and storage of biological specimens for genetic or molecular analysis in this trial/future use {33}

Two microbial samples will be taken (using CE (conformité européenne) marked IVD’s (invitro diagnostics)) from the esophageal resection specimen (one proximal and one from the distal part) for culture to evaluate effectiveness and compliance of SDD application in control as well as in the intervention group. All responsible laboratories have ISO (International Organization for Standardization) 15189 certification. After analyses the samples are destroyed according to local laboratory protocols.

### Statistical methods

#### Statistical methods for primary and secondary outcomes {20a}

The primary analysis will be according to intention to treat, including all randomized participants. Per protocol analyses will be performed in patients that received SDD or no SDD in accordance with the randomized allocation. For the analysis of the primary outcome, we will use Cox regression (cause-specific hazard ratio which defines the effect on the daily hazard), with censoring for death and putative loss to follow-up, and we will adjust for the stratification variables by including these as strata in the regression. A sensitivity analysis will be performed using Fine and Gray regression (sub distribution hazard ratio which defines the effect on cumulative incidence) considering mortality as competing events and censoring for putative loss to follow-up, also including the stratification variables as strata.

Secondary outcomes will be analyzed using logistic regression (all-cause mortality and rate of re-operation), time-to-event analysis (incidence using Cox regression and cumulative incidence using Fine and Gray regression), or linear regression (length of stay and quality of life), as appropriate.

### Interim analyses {21b}

We will use a group-sequential design for the analysis of the primary endpoint, based on asymmetric testing design (superiority and futility). Analysis of the primary endpoint will take place after 30% (*N* = 257) and 60% (*N* = 513) of the patients have been included. If these interim analyses lead to an unambiguous conclusion on the effectiveness or futility of the intervention, this may cause an adjustment or early termination of the trial.

### Methods for additional analyses (e.g., subgroup analyses) {20b}

Explorative subgroup analyses will be performed to assess differences in efficacy between men and women and age groups.

### Methods in analysis to handle protocol non-adherence and any statistical methods to handle missing data {20c}

The amount of missing data will be described. Missing data in variables that are planned to be included in multivariable models will be imputed using multiple imputation. Missing outcome variables and missing data in planned subgroup variables will not be imputed.

### Plans to give access to the full protocol, participant-level data and statistical code {31c}

The study protocol is made available to the public on ClinicalTrials.gov under reference https://clinicaltrials.gov/study/NCT05865743.

### Oversight and monitoring

#### Composition of the coordinating center and trial steering committee {5d}

At both coordinating centers, a PhD candidate and a research coordinator oversee the trial’s daily operations under the supervision of two principal investigators. Biweekly evaluations are conducted with the trial steering committee, with additional consultations available throughout the week. Additionally, an adjudication committee has been established to analyze the primary endpoint. This adjudication committee is composed of 3 unbiased non-blinded experts that will meet after 30% and 60% of participants have completed follow-up of 30 days after surgery, and after completion or termination of the trial.

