### Outcomes {12}

#### Primary outcome

The primary outcome parameter is the cumulative incidence of postoperative pneumonia within 30 days after surgery. Pneumonia will be defined by the following criteria: positive sputum culture or the presence of a new progressive radiographic infiltrate plus at least two of the following clinical features: fever > 38.5 °C, leucocytosis (> 11.0*10^9/L) or leukopenia (< 4.0*10^9/L), or purulent secretions.

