## Discussion

Esophagectomies are often followed by (infectious) complications, especially pneumonia. To reduce the risk of pneumonia, some hospitals in the Netherlands already use SDD. However, the scientific evidence remains limited. The large studies demonstrating the safety and efficacy of SDD in reducing infectious complications and mortality were never conducted in esophageal patients. These trials primarily involved patients in intensive care units or those undergoing elective (mostly lower) gastrointestinal surgery [14, 29, 30]. To date, little evidence exists regarding the perioperative use of SDD in esophageal cancer surgery. The few studies addressing this population are generally observational, vary in SDD composition and duration and are often small or of lower quality.

We designed a large, open-label randomized controlled trial comparing standard care with SDD to standard care without SDD, to find the much-needed evidence on the efficacy of SDD in patients undergoing esophageal cancer surgery. We selected the most widely used SDD formulation, combining amphotericin-B, colistin and tobramycin to target not only the most common bacterial pathogens, namely gram-negative rods, but also yeasts. Our study does have some limitations. A key point to consider is that no placebo will be used in our trial. Patients receiving SDD in addition to standard care will be compared to a control group receiving standard care without a placebo. Incorporating a placebo in this large, investigator-initiated drug trial was deemed impractical, as a significant portion of the intervention occurs at home without study staff supervision. This design reflects a real-life scenario, in contrast to the potential selection bias that may arise in placebo-controlled trials. However, the absence of a placebo increases the risk of biased outcome assessment. To mitigate this, we have implemented objective criteria for the primary endpoint. Furthermore, global shortages of SDD components may require adjustments to the composition of our investigational medicinal product (IMP). However, a suitable alternative is available, and such modifications also occur in clinical practice. Therefore, the intervention remains well-defined and reflective of real-world conditions, making the intervention sufficiently well-defined.

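### The experts who adjudicate pneumonia are stated to be unblinded, which must be reconciled with the promised blinded outcome analysis and leaves case classification open to knowledge of allocation

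*Protocol article*

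**What the plan says.** The protocol article addresses this in four places.

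- **Blinding, {17a} and {17b}.** The first section states "As an open label study, allocation of the intervention will not be blinded" and then "Analysis of the outcome parameters will be blinded". The second repeats it: "The analysis of the outcome parameters will be blinded". Neither says which people are blinded or at which step.
- **Coordinating center and steering committee, {5d}.** Here "an adjudication committee has been established to analyze the primary endpoint", and "This adjudication committee is composed of 3 unbiased non-blinded experts". The committee meets once 30% and 60% of participants have completed 30-day follow-up, and again at the end of the trial.
- **Primary outcome, {12}.** Pneumonia is defined by "positive sputum culture or the presence of a new progressive radiographic infiltrate plus at least two of the following clinical features". The features are temperature and leucocyte count, each with a numerical cut-off, and purulent secretions.
- **Discussion.** The article concedes that "the absence of a placebo increases the risk of biased outcome assessment" and gives as mitigation that "we have implemented objective criteria for the primary endpoint". Masked adjudication is not mentioned.

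Two further sections bear on the point. Primary endpoint data come from the medical records ({18a}), and the monitor checks the primary outcome against those records for all trial patients ({19}).

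**The concern.** Patients and treating staff know the allocation, and the endpoint data come from records kept under that open-label care. Expert adjudication is a natural place to put masking back, because the experts work from documents and do not need to know the arm. The plan states outright that they are not blinded, so this is not a detail left to a charter.

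Two parts of the definition call for judgement: whether an infiltrate is new and progressive, and whether secretions are purulent. Borderline cases turn on these. If knowing the arm tilts such calls even slightly, the tilt enters the event counts used at the interim looks and in the final comparison. Neither a stratified Cox model nor a blinded statistician can remove bias already built into the case labels. Describing the experts as unbiased asserts a quality but provides no safeguard.

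**Working it through.** **Step 1: the texts side by side.** Sections {17a} and {17b} call analysis of the outcome parameters blinded. Section {5d} gives analysis of the primary endpoint to a non-blinded committee. There are three ways to read them together:

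| Reading | Consequence |
|---|---|
| Analysis means the same activity in both places | The sections conflict |
| {17a}/{17b} mean only the statistician's work, and {5d} means case adjudication | No literal conflict, but cases are classified with allocation known |
| Non-blinded in {5d} is a slip for blinded | {5d} is wrong as printed |

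Each reading requires a change to the text. The article does not say which is meant, and no section hides allocation from the adjudicators.

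**Step 2: the plan's own sample size.** Sample size {14} gives 22% in controls, a 40% reduction, 90% power, two-sided alpha 0.05 and 407 per arm. The exact reduction is 0.22 × (1 − 0.40) = 0.132. A fixed two-proportion design (pooled variance) needs 392 per arm at 13.2%, or 373 at the rounded 13%. The spending parameter is not stated. With assumed Hwang-Shih-DeCani parameters of −4 for efficacy and −2 or −4 for futility, the inflation factor for looks at 30% and 60% is 1.022 to 1.061. That gives 392 × 1.022 ≈ 401 to 392 × 1.061 ≈ 416 per arm, so 407 is consistent with the plan. It is used below only as an input.

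**Step 3: illustration of sensitivity.** Assumptions, none of which the documents supply:

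- no true effect, with 22% true pneumonia in both arms;
- adjudicators reject a fraction f of true cases in the SDD arm only;
- one fixed test at 1.96, ignoring the interim looks and the planned stratified Cox model.

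Expected true cases per arm are 407 × 0.22 = 89.5. With p1 = 0.22, p2 = 0.22(1 − f), d = p1 − p2 and p̄ = (p1 + p2)/2:

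- SE0 = √[2p̄(1 − p̄)/407]
- SE1 = √[(p1(1 − p1) + p2(1 − p2))/407]
- P(false superiority) = 1 − Φ[(1.96·SE0 − d)/SE1]

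| f | Cases rejected | p2 | d | SE0 | SE1 | Argument of Φ | P |
|---|---|---|---|---|---|---|---|
| 0 | 0 | 0.220 | 0 | – | – | 1.960 | 2.5% |
| 5% | 4.5 | 0.209 | 0.011 | 0.02877 | 0.02877 | 1.578 | 5.7% |
| 10% | 9.0 | 0.198 | 0.022 | 0.02850 | 0.02849 | 1.189 | 11.7% |

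With an assumed final critical value of 2.0 in place of 1.96, the last two results become about 5% and 11%.

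**Step 4: the other direction.** If the rejected cases are in the control arm instead, the arms swap. The chance of a false superiority claim then falls to about 1.0% (f = 5%) or 0.3% (f = 10%), and a real benefit would be harder to show.

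**The case against.** The strongest case on the other side has five parts.

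1. **Flat contradiction.** A reader might infer that {5d} plainly contradicts {17a} and {17b}. The text does not force this: blinded analysis can mean the statistics, and the committee's work is adjudication. This stands, so the wording is unclear rather than demonstrably contradictory. The need to reconcile it remains, because {5d} itself uses the verb analyze for the committee's task.
2. **Only remaining step.** A reader might say that adjudication is the only point at which blinding could be restored. The documents do not support that. Masked reading of images, masked extraction from records and a masked statistician are also possible, and {17a}/{17b} may already promise the last.
3. **Uninterpretable result.** A reader might conclude that a positive result could not be told apart from assessment bias. That goes too far. Temperature and leucocyte cut-offs are fixed, sputum culture is a laboratory result, and the monitor checks the primary outcome for every patient. These safeguards blind no one, but they limit free reclassification.
4. **Committee authority.** The article does not say whether the committee's verdict overrides the site record. This stands, and it is a reason to state it.
5. **Illustration.** The bias is put in one direction, and f applies to all SDD-arm cases although only borderline ones are in question. Larger values of f would be hard to square with the fixed thresholds. The figures show sensitivity and are not evidence that bias will occur.

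**Conclusion.** The point holds in a bounded form. The plan states that the committee for the primary endpoint is not blinded, while other sections promise blinded analysis of outcomes. The text must be reconciled on any reading. If the promise covers only the statistician, classification with knowledge of allocation remains an avoidable source of bias on the primary endpoint, in a trial whose own Discussion concedes the risk. The objective features of the definition and the monitor's check reduce that risk without removing it.

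The size and direction of any bias cannot be known from the document. Under the stated assumptions, four to nine reclassified cases out of about 90 in one arm would roughly double to nearly quintuple the one-sided error of 2.5%. That is enough to justify an inexpensive correction. It does not show that the trial's result will be biased or uninterpretable.

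**What to change.** - **Section {5d}:** state that the same three experts are blinded to allocation.
- **Dossiers:** supply every element of the pneumonia definition, namely sputum culture, imaging, temperature, leucocytes and secretions, with dates. Remove the allocation, SDD administration and accountability records, the diary and the resection-specimen swab results.
- **Status of the verdict:** state that this blinded classification is the primary endpoint at both interim analyses and the final analysis.
- **Cases already adjudicated:** re-read them from masked dossiers.
- **Sections {17a} and {17b}:** state who is blinded, to what and at which step.

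**Cost and limits.** Existing staff must redact records from many sites, and the change needs an amendment; the article routes substantial modifications through CTIS. Recruitment began in October 2024 and is expected to run to December 2027, so the change can still cover much of the trial. Sample size, treatment and follow-up are unaffected. Masking may be imperfect: SDD targets gram-negative rods and yeasts, so culture results may partly hint at the arm. It also does not correct open-label decisions about which tests are ordered and what is recorded.

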### Composition of the data monitoring committee, its role and reporting structure {21a}

To monitor safety, futility and efficacy, an independent Data Safety Monitoring Board (DSMB) is appointed. A DSMB charter is created according to DAMOCLES guidelines [28]. The DSMB will have access to the gathered primary and secondary endpoint data. The DSMB will review the cause of death from all deceased patients to evaluate possible relations to the study intervention. The board consists of a statistician, an intensivist/toxicologist and a surgeon to ensure a comprehensive assessment of the data from multiple clinical and methodological perspectives. After every meeting, the DSMB will report to the trial steering committee to discuss results. The DSMB’s advice will be sent to the Principal Investigators of the sponsor institute supervising the trial in the Netherlands and the Belgian coordinating center. Should these PIs decide not to fully implement the advice of the DSMB, the sponsor will send the advice to the reviewing METC, including a note to substantiate why (part of) the advice of the DSMB will not be followed.

